## Abstract

**Background:** Impairment of upper limb function following stroke is more common than lower limb impairment and is also more resistant to treatment. Several lab-based studies with stroke patients have produced statistically significant gains in upper limb function when using musical instrument playing and techniques where rhythm acts as an external time-keeper for the priming and timing of upper limb movements.

**Methods:** For this feasibility study a small sample size of 14 participants (3–60 months post stroke) has been determined through clinical discussion between the researcher and study host in order to test for management, feasibility and effects, before planning a larger trial determined through power analysis. A cross-over design with five repeated measures will be used, whereby participants will be randomized into either a treatment (*n* = 7) or wait list control (*n* = 7) group. Intervention will take place twice weekly over 6 weeks. The ARAT and 9HPT will be used to measure for quantitative gains in arm function and finger dexterity, pre/post treatment interviews will serve to investigate treatment compliance and tolerance. A lab based EEG case comparison study will be undertaken to explore audio-motor coupling, brain connectivity and neural reorganization with this intervention, as evidenced in similar studies.

**Discussion:** Before evaluating the effectiveness of a home-based intervention in a larger scale study, it is important to assess whether implementation of the trial methodology is feasible. This study investigates the feasibility, efficacy and patient experience of a music therapy treatment protocol comprising a chart of 12 different instrumental exercises and variations, which aims at promoting measurable changes in upper limb function in hemiparetic stroke patients. The study proposes to examine several new aspects including home-based treatment and dosage, and will provide data on recruitment, adherence and variability of outcomes.

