### Procedure

Each participant will have a total of 12 individual music therapy sessions in their home, delivered twice weekly over the course of 6 weeks. They will not be required to perform any practice or exercises set by the researcher between sessions. Whilst in wait list, before the intervention begins, participants will not receive any community nor privately employed rehabilitation interventions for upper limb hemiparesis. Each participant will also receive the Action Research Arm Test (ARAT) (Lyle, 1981) and Nine Hole Peg Test (9HPT) (Kellor et al., 1971) assessments at the same five time points after baseline measure, over an 18 week period as follows: Timepoint 1 at Week 1 after randomization; timepoint 2 at week 6; timepoint 3 at week 9; timepoint 4 at week 15; and timepoint 5 at week 18. The design will allow analysis of treatment and no treatment by comparing treatment group with wait list group data. It will also be possible to compare early versus late intervention following discharge from the community rehabilitation treatment, as the wait list participants will have a delay of 9 weeks between community discharge and beginning TIMP. Data collected from wait list group participants prior to TIMP treatment will be analyzed to determine whether there has been any spontaneous change in upper limb function, which can occur as an independent covariate (Kwakkel et al., 2006). Subject data from the ARAT and 9HPT will also be individually analyzed in order to discuss group results.

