Although unusual in a randomized cross-over design study, qualitative data will be collected from each participant in order to explore patient preference with regard to using music to support exercises, and factors that might provide insights into patient tolerance and compliance. These aspects are important given the innovative treatment being used, the dosage and the setting i.e., within the home environment. Qualitative data will be collected by the researcher immediately before and after the 6 weeks of TIMP, by using a semi-structured interview that has been devised for this study and comprises five questions regarding the participant's experience of playing the instruments and playing to the music. This data will provide an overall impression of the feasibility for this treatment protocol. Participant responses to the post semi-structured interview will specifically provide data regarding motivational effects. In addition, the researcher will gather information in a research journal during and after each session, which will describe emotional responses; no direct quotes from participants will be used. There is also a five point Likert scale for recording how much participants feel the treatment will help them and, at the end of the 6 weeks of TIMP, how much they feel it actually has helped them in their ADLs. The researcher will record, in written form, participants' responses during the interview for later thematic analysis. Open questions will be used to give participants the opportunity to express their preconceptions and communicate their experience of the treatment, with the possibility of other themes arising. The quantitative data gained with the Likert response scale is used to record a time series of treatment responses (control for auto-correlation is not intended).

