### Sample size

The sample size of 14 stroke patients was calculated not based on a power calculation but through discussion of clinical matters between the researcher and the NHS trust hosting the study. The discussion was based on defining an appropriate number of stroke patients that would represent the heterogeneity of upper limb impairment and facilitate a report on the feasibility, management and efficacy of the intervention under the stated research conditions (unknown music based treatment, in participants' homes, twice weekly). The sample size is considered feasible for the researcher to deliver with the available time scale and resources within the host NHS trust, including staff assisted access to patient records, identification of suitable patients and invitation to participate from NHS community stroke team therapists, and completion of data collection within a limited period of time. Risks, benefits and the logistics of delivering treatment in the home, given that it is labor intensive and delivered by the researcher alone, will be observed and reported, together with participant compliance. The home environment will introduce variables that cannot be controlled for, such as space available to set up equipment, management of seating equipment to optimize positioning for the intervention, distractions in sessions such as the activities of family members or other residents present in the home. The instruments will not be set up permanently, as would be the case in a research lab, where instrument height and distance from participant can be maintained and standardized. In this study TIMP will be delivered at a frequency much lower than has been the case in existing research of this nature, so effects at this dosage are not known. All of these logistical factors warrant detailed examination in a smaller feasibility study prior to moving to a study with a larger number of participants.

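### The sole treating therapist also conducts and writes up the pre/post interviews on tolerance, compliance and feasibility, so post-treatment answers are likely to lean favourable; a sealed self-completed rating would be a cheap partial safeguard.

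*Protocol article*

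**What the plan says.** All quotes are from the protocol article.

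- **Who treats.** Procedure: "Each participant will have a total of 12 individual music therapy sessions in their home". Sample size describes home delivery as a logistical burden, "given that it is labor intensive and delivered by the researcher alone".
- **Who interviews, and when.** Procedure: "Qualitative data will be collected by the researcher immediately before and after the 6 weeks of TIMP".
- **Who makes the record.** Procedure: "The researcher will record, in written form, participants' responses during the interview for later thematic analysis". The article mentions no audio recording of the interviews.
- **The rating.** Same paragraph of Procedure: "There is also a five point Likert scale for recording how much participants feel the treatment will help them". After the six weeks it is asked again as help actually experienced in daily activities. The article does not say who hands the scale out or who marks it.
- **What the interviews are for.** Abstract: "pre/post treatment interviews will serve to investigate treatment compliance and tolerance". The Background adds motivation and access. Procedure says these data give an overall impression of feasibility, and the section on semi-structured interviews says the feedback feeds into feasibility questions.
- **What else informs feasibility.** The Abstract lists recruitment, adherence and variability of outcomes. Sample size adds observed logistics, risks, benefits and compliance.
- **Where there is protection.** The blinded assessor and the blinding script (Study design, Figure 1 legend, Participants) concern the ARAT and 9HPT assessments.

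**The concern.** After six weeks of individual therapy, participants are asked how they found it, and the therapist who gave it does the asking. They have an ordinary social reason to be kind. The person taking the notes developed and delivered the treatment and cannot be neutral about the answer. Because the record is a written note made during the interview, a reader cannot later separate what was said from what was noted.

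Feasibility is a lead aim of this study, and its results are meant to inform a larger trial. If reported tolerance, motivation and perceived help are too favourable, the larger trial may be planned on an optimistic view of acceptability. This kind of bias does not average out with more participants. The plan already guards against assessor expectation for the two performance tests. The participant-reported data, which are more open to courtesy bias, have no comparable safeguard described.

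**Working it through.** The documents give no figure for this bias and none from which it could be derived, so the check sets the sections side by side.

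1. **Are therapist and interviewer the same person?** Yes, as stated. Sample size says the researcher alone delivers the treatment, and Procedure says the researcher collects the qualitative data immediately before and after it. This needs no inference.

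2. **Does the same person make the raw record?** Yes, as stated in Procedure.

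3. **Do conclusions rest on these data?** In part. The Abstract, Background, Procedure and semi-structured interviews sections tie the interviews to compliance, tolerance, motivation and feasibility. The Abstract and Sample size show that recruitment, adherence and logistics contribute as well.

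4. **Is there independently collected evidence on tolerance?** None is described. The session journal (Procedure) and the questions about pain and discomfort (Monitoring patient performance) also come from the researcher. Attendance at the 12 sessions is a count, and so is less open to courtesy.

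5. **Is the rating taken face to face by the researcher?** Not stated. Its place in the interview paragraph suggests the same setting, but that is inference.

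6. **Which way would the bias go?** For post-treatment answers, a favourable shift is the likely direction. The pre-treatment rating is presumably taken in the same way, but it asks about expectation and comes before the 12-session relationship has formed. The two shifts need not be equal and need not cancel, so the direction for the pre/post difference cannot be fixed.

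7. **Scale, for illustration only.** Suppose k of the 14 participants each rate one category higher than they would in private. The mean rises by k × 1/14.
   - k = 1: 1/14 = 0.07 points
   - k = 0: 0 points
   - k = 14: 14/14 = 1.0 point

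   The documents do not narrow k within 0 to 14, so on this assumption the shift lies anywhere from 0 to 1.0 point on the five-point scale. The article does not say that a mean rating will be reported, so this is not an estimate of error in a planned result.

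**The case against.** **The plan is open about its limits.** This is a 14-person feasibility study run by one researcher with limited resources, and Sample size says so. A second interviewer needs staff time, and using the blinded assessor would risk unblinding. This stands, and it is why no independent interviewer is asked for.

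**The rating may already be self-completed.** The article does not say how the scale is administered, and an article may leave that to the full protocol. This stands too. A reader might infer from the paragraph that the therapist takes the rating face to face, but the text does not say it. If the full protocol already has private completion, the request reduces to saying so.

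**The remedy does not match the harm.** The interviews carry tolerance and compliance, while the scale asks about help in daily activities. Sealing the scale does not repair the interviews, and a form cannot replace open questions analysed by interpretative phenomenological analysis. This is correct. The sealed form protects only the perceived-benefit data, and the interviews get a weaker remedy.

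**Reliance is easily overstated.** A reader might conclude that feasibility and tolerance rest on the interviews alone. The documents do not support this, because recruitment, adherence and logistics are also reported.

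**Other tempting readings.** A reader might assume that the researcher also does the thematic analysis, or that the interviews take place in the participant's home. The article names neither the analyst nor the place, and the point does not depend on either.

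**Conclusion.** The point holds in a limited form. As written, one person delivers all treatment, conducts the pre/post interviews and writes down the answers, and no safeguard or limitation is described for those data. A favourable shift in the post-treatment answers is likely. The rating is probably exposed to the same risk, on the assumption that it is taken in the interview setting.

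The size is unknown. A firm claim that the results will be biased upward by a given amount would go beyond the documents, and so would a claim about the direction of the pre/post change. The ARAT primary outcome is not affected, and feasibility has other sources of evidence. The issue is therefore one to consider: a modest, inexpensive improvement to participant-reported data that serve a lead aim.

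**What to change.** **Rating (Procedure).** State that at both time points the participant completes the five-point item on paper, out of the researcher's sight and before the interview. The form goes into a sealed envelope that is not opened until data collection ends. Report this as the patient-rated benefit.

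**Interviews (Procedure and Semi-structured interviews).** Keep them researcher-led and report them as therapist-collected. Interpret tolerance and compliance together with the adherence records. If ethics allow, audio-record the interviews so that the thematic analysis rests on participants' own words and not on notes.

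**Cost.** The rating change takes paper forms, envelopes and a line or two of procedure. It should need no extra staff, although the documents do not address this. Audio recording would need ethics agreement and time for transcription.

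**Downside.** The Background describes varied cognitive, sensory and communication impairments in this patient group, besides the weak arm. Some participants will need help with the form. The helper should be someone other than the researcher, and the help should be noted on the form, because a helper can also influence the answer.

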### Recruitment

Participants will be recruited from three geographically separate community stroke rehabilitation teams in the south of England. Patients discharged from community rehabilitation who meet the inclusion criteria will be invited by the host NHS trust to participate in this study. It will not be possible to control for the length of time that each participant receives statutory community rehabilitation prior to joining the study, as within the host NHS trust this is extremely variable. Music therapy is also not recognized as an intervention for upper limb hemiparesis following stroke in the UK. As such, the host NHS trust cannot agree to facilitate any disruption or adjustment to standard treatment for their patients for music therapy research purposes. Such bodies as the Care Quality Commission (CQC) (Care Quality Commission, 2011) and National Institute for Clinical Excellence (NICE) (National Institute For Health and Care Excellence, 2013) do not recommend music therapy as an intervention with stroke patients. However, following a review of music therapy and traumatic brain injury by the Cochrane library, music therapy is now listed as a possible intervention within neurorehabilitation (Bradt et al., 2010). Potential participants who meet the inclusion criteria and, following invitation by the host NHS trust, have expressed an interest in the study will be visited in their home by the researcher in order to demonstrate the treatment methods, including the playing patterns, and answer any questions. All participants will be required to give informed consent, which will be recorded.

### Participants

Fourteen adult participants, 3–60 months post stroke, with hemiparesis will be recruited who have been discharged from community rehabilitation and can consent to treatment. The age range for inclusion will be 18–90. As with the MST studies (Schneider et al., 2007; Altenmüller et al., 2009; Rojo et al., 2011; Amengual et al., 2013) participants must be able to lift their affected hand up on to a table whilst seated, unaided by their unaffected side and have some finger movement in the affected hand. In a meta-analysis of literature reporting prognostic variables in upper limb recovery (Coupar et al., 2012), inconclusive evidence was found for time since stroke being a predictor. Comparisons between lesion site also revealed no predictive value in upper limb recovery. The most significant findings were that patients recovered significantly more upper limb function if there was less impairment in their upper limb initially caused by the stroke. The inclusion criteria for this feasibility study has been determined based on this research and that set for the MST studies earlier cited. On entry into the study participants will be randomized to either the treatment or wait list group, with a list of numbers randomly generated by an independent statistician using a computer, which will be concealed using opaque sealed envelopes. The assessor will be blinded to participant allocation. In order to maintain blinding the researcher will deliver a script for all participants and the assessor at each assessment time-point.

### Sample size

The sample size of 14 stroke patients was calculated not based on a power calculation but through discussion of clinical matters between the researcher and the NHS trust hosting the study. The discussion was based on defining an appropriate number of stroke patients that would represent the heterogeneity of upper limb impairment and facilitate a report on the feasibility, management and efficacy of the intervention under the stated research conditions (unknown music based treatment, in participants' homes, twice weekly). The sample size is considered feasible for the researcher to deliver with the available time scale and resources within the host NHS trust, including staff assisted access to patient records, identification of suitable patients and invitation to participate from NHS community stroke team therapists, and completion of data collection within a limited period of time. Risks, benefits and the logistics of delivering treatment in the home, given that it is labor intensive and delivered by the researcher alone, will be observed and reported, together with participant compliance. The home environment will introduce variables that cannot be controlled for, such as space available to set up equipment, management of seating equipment to optimize positioning for the intervention, distractions in sessions such as the activities of family members or other residents present in the home. The instruments will not be set up permanently, as would be the case in a research lab, where instrument height and distance from participant can be maintained and standardized. In this study TIMP will be delivered at a frequency much lower than has been the case in existing research of this nature, so effects at this dosage are not known. All of these logistical factors warrant detailed examination in a smaller feasibility study prior to moving to a study with a larger number of participants.

### Measures

A wide range of assessment tools and technology has been used to record outcomes in upper limb post-stroke rehabilitation. The selection of assessment tools for this feasibility study has been determined by two major factors: (1) the restrictions enforced by the ethics committee who approved the study according to UK ethics procedures for research within the NHS via the Integrated Research Application System (IRAS), (2) availability of assessment tools and training requirements for their application. The Action Research Arm Test (ARAT), will be the primary outcome measure for this study; 9HPT will measure finger dexterity and semi-structured interviews allow for the collection of qualitative data on the participant experience. The ARAT has also been used in constraint-induced movement therapy studies (Kitago et al., 2013), and a study using rhythm and music with stroke patients (Bunketorp Kall et al., 2012). It has excellent inter-rater reliability (Hsieh et al., 1998; van der Lee et al., 2002), excellent intra-rater reliability (van der Lee et al., 2002), and excellent convergent validity against the Fugl-Meyer (De Weerdt, 1985). The ARAT is a timed, 19 item measure that is divided into four categories: grasp, grip, pinch and gross movement. Each item, or action, is performed by the participant while seated with their back against the chair, a measured distance from the table (15 cm), where all of the assessment items are individually placed for each task (see Figure 2). The test recreates the movements or sequences of movements required to perform many ADLs, such as reaching up onto a shelf to obtain a food ingredient or pouring liquid from one container to another. A table map for the ARAT is laid out flat on the table top and this has markers on it to indicate the start and end position for each object used in the test, thus optimizing consistency between patients and settings. The assessment can take up to 30 min if the patient needs to complete all items in every subcategory.

**Figure 2 F2:**
[figure not shown]
**The action research arm test**.

The 9HPT, more specifically measuring finger dexterity, is widely used in stroke rehabilitation and related research (Kellor et al., 1971). It has excellent inter-rater reliability and adequate intra-rater reliability (Oxford Grice et al., 2003). It is a timed test, using standardized equipment comprising a rectangular plastic tray with a rounded, concave tray at one end containing nine small white pegs and at the other end nine holes into which the participant must (one at a time) place the nine pegs from the tray and then remove them, placing them back into the tray as quickly as possible. The participant practices with the unaffected hand first, then the affected side. The participant is seated while performing the test, which takes no more than 2 minutes to administer, depending on the age of the patient and their existing degree of finger dexterity.

